### Sample size calculation

A total of 2600 new TB patients will be eligible and consent to be screened for alcohol misuse over a period of six months. Assuming that 20% screen positive for problem drinking, 520 new TB patients will enter the study. A minimum of 13 patients will be recruited from each of the 42 primary care clinics. It is expected that 10% of participants may be lost prior to completing the 3-months and 6-months follow-up assessments so that the final sample would be 468.

Based on the current AUDIT score of 12 among TB patients, it is assumed that the intervention will reduce the current AUDIT score by 12% to 10.6 [32,33]. Based on this assumption and taking account of the design effect of 2 to account for intraclass correlations expected from participants from the same area and followed up over time the estimated sample size of 452 will allow us with 80% power (5% level of significance) to detect the difference of 12% between the two groups.

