#### Analysis approach

The primary outcome will be measured at three time points: baseline, three and at six months. If a patient drops out, is not present on the day of the interview or refuses to answer questions the primary outcome at the end point of the trial will be missing. Therefore, except for the baseline measurement, no post-randomization information will be available for these participants. The extent of the missing component was estimated to be 10% at six months. The single follow-up measurement and the extent of the expected dropout has to be considered for the statistical method that can be used to provide an unbiased estimate of the intervention effect under the principle of intention to treat. The method that can be used to take account of the stratified cluster trial design, the repeated binary nature of the primary and secondary outcome (Risky drinking, TB treatment adherence, TB treatment outcome) and the missing data at follow-up is a weighted generalized estimation equations (WGEE) approach [35]. The method utilizes inverse probability weighting to correct for the bias associated with missing data that is not missing completely at random (MCAR) and participants with complete data are weighted with the dropout probability of participants with the same characteristics at baseline. To determine the weights a logistic regression model will be constructed for the dropout indicator utilizing measurements on the primary outcome (at baseline) and other variables taken at baseline or post-randomization. For comparison and checking an unweighted analysis will also be done.

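### The plan names inverse probability weighting but describes a completer's weight as the dropout probability, not the inverse of the probability of being observed

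*Protocol article*

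**What the plan says.** All of the relevant text is in the Analysis approach section of the protocol article. It chooses weighted GEE as the way to an unbiased intention-to-treat estimate when some follow-up is missing. The purpose of the weights comes first: "The method utilizes inverse probability weighting to correct for the bias associated with missing data that is not missing completely at random (MCAR"). The same sentence then describes the weight itself: "participants with complete data are weighted with the dropout probability of participants with the same characteristics at baseline". The next sentence gives its source: "To determine the weights a logistic regression model will be constructed for the dropout indicator", with the baseline primary outcome and other baseline or post-randomization variables as predictors.

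On the amount of missing data the section says "The extent of the missing component was estimated to be 10% at six months". It also plans a cross-check: "For comparison and checking an unweighted analysis will also be done".

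Nowhere does the article give the weight as 1/(1 - dropout probability) or refer to the probability of being observed.

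**The concern.** Inverse probability weighting lets each completer stand for similar patients who were lost. If a patient of a given type is observed with probability 1 - p, each observed patient of that type represents 1/(1 - p) patients, and that is the weight. The article names the method and then describes a different quantity, p, so the sentence contradicts itself.

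The slip matters because p and 1/(1 - p) are far from proportional when dropout is low. Between patients with 5% and 15% dropout risk, 1/(1 - p) rises by a factor of 1.12 and p by a factor of 3. The logistic model of the dropout indicator outputs p, so a programmer could use p directly, or apply the word inverse to it and use 1/p. The first over-weights patients who resemble dropouts. The second down-weights the patients who should count for more. This is the designated analysis; the unweighted one serves only as a check.

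**Working it through.** **The plan's own figures.** From Sample size calculation: 2600 × 0.20 = 520 enrolled, and 520 × (1 - 0.10) = 468, which matches "so that the final sample would be 468". The 10% agrees with the six-month figure in Analysis approach. The document gives no numerical weight and no dropout rate by patient type, so what follows is illustration.

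**Assumptions (not in the document).** Two strata of equal size, with dropout p1 and p2 averaging 10%. Risky drinking is 40% in the low-dropout stratum and 70% in the high-dropout stratum, so the true rate is 0.5 × 0.40 + 0.5 × 0.70 = 55.0%. There is one follow-up visit, and arm is the only covariate in the outcome model.

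**Formula.** Completers in stratum s make up c_s = 0.5 × (1 - p_s) of those enrolled. The weighted rate is Σ c_s w_s m_s / Σ c_s w_s, where m_s is the stratum's rate and w_s its weight.

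**5%/15% split.** c1 = 0.475, c2 = 0.425.

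- Unweighted: (0.475 × 0.40 + 0.425 × 0.70) / 0.90 = 54.2%.
- w = 1/(1 - p), that is 1.053 and 1.176: both products c_s w_s return to 0.5, giving 55.0%.
- w = p: products 0.02375 and 0.06375, giving (0.00950 + 0.04463) / 0.0875 = 61.9%.
- w = 1/p: products 9.5 and 2.833, giving (3.8 + 1.983) / 12.333 = 46.9%.

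**Range over splits (true rate 55.0%).**

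| Dropout split | Unweighted | 1/(1 - p) | p | Weight ratio, 1/(1 - p) | Weight ratio, p |
|---|---|---|---|---|---|
| 10/10 | 55.0% | 55.0% | 55.0% | 1.00 | 1.0 |
| 8/12 | 54.7% | 55.0% | 57.7% | 1.05 | 1.5 |
| 5/15 | 54.2% | 55.0% | 61.9% | 1.12 | 3.0 |
| 2/18 | 53.7% | 55.0% | 66.5% | 1.20 | 9.0 |

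**Precision, 5%/15% split.** The effective sample size as a share of completers is (Σ c_s w_s)² / (0.90 × Σ c_s w_s²). For w = p it is 0.0875² / (0.90 × 0.01075) = 79%. For w = 1/(1 - p) it is 1 / (0.90 × 1.1146) = 99.7%.

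**Effect on the treatment odds ratio.**

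- Same 5%/15% dropout in both arms, odds ratio 0.6 in each stratum: true marginal 0.629, unweighted 0.629, weight p 0.623. Almost no change.
- Same dropout in both arms, odds ratio 0.5 in the low-dropout and 1.0 in the high-dropout stratum: true 0.740, unweighted 0.728, weight p 0.844.
- Dropout 10%/10% in control and 5%/15% in intervention, no true effect: under weight p, control is 55.0% and intervention 61.9%, so the odds ratio is (0.6186/0.3814) / (0.55/0.45) = 1.33. Unweighted gives 0.97 and 1/(1 - p) gives 1.00.
- Same dropout as the previous case, odds ratio 0.6 in each stratum: true 0.629, unweighted 0.608, weight p 0.827.

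The last two results assume that the dropout model lets the pattern differ by arm. If it pooled the arms, the modelled p would be 7.5% and 12.5%. Weight p would then give 58.75% in control and 57.96% in intervention, a null odds ratio of (0.5796/0.4204) / (0.5875/0.4125) = 0.97, about the same as unweighted.

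**The case against.** The strongest defence is that the clause is shorthand. The same sentence names inverse probability weighting, the estimator is a cited weighted GEE method, and 1/(1 - p) follows at once from a dropout model. An experienced analyst would probably program it correctly. The article is condensed, and the exact formula may stand in an analysis plan that is not shown. The unweighted comparison would probably expose a gross weighting error.

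Most of this stands and limits the severity. It does not remove the point: an article may leave the formula out, but this one describes the weight and describes it wrongly. Nor is the comparison a complete safeguard, because a gap between the two analyses could be read as dropout bias that the weights had removed.

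Four stronger readings are tempting and are not supported.

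- **That the weighted analysis will be grossly biased.** This needs the clause to be programmed literally. It also needs dropout patterns that differ by arm (and are modelled so) or effects that vary with dropout risk.
- **That 1/p would be worse than p.** The order depends on the strata. In the example above 1/p misses the rate by 8.1 points and p by 6.9. Now take 80% of patients at 6.25% dropout and 20% at 25%, which also averages 10%. Completer shares are 0.75 and 0.15. The high-risk share, truly 20%, becomes 0.0375/0.0844 = 44.4% under p and 0.6/12.6 = 4.8% under 1/p, so p is further off.
- **That the article claims to correct every departure from MCAR.** It does not say so; it ties the weights to patients alike at baseline and to modelled variables. Stating that condition openly is a useful clarification, not the repair of a false claim.
- **That missing covariate lists or visit-specific weights are a fault.** That detail may be left to the analysis plan, and the article already allows baseline and post-randomization predictors.

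**Conclusion.** The description of the weight is wrong as written and conflicts with the method named in the same sentence. Severity is minor to moderate. No sample size, power figure, outcome or data collection is affected.

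The harm is conditional. Programmed literally, weight p over-weights patients who resemble dropouts and loses precision, and it can be further from the truth than no weighting. In the illustrations it moves the risky-drinking rate by 0 to 11.5 points (66.5 - 55.0 at the widest split) and a null odds ratio to at most 1.33. These sizes rest on the assumed strata, rates and arm-specific weights; the document supplies only the 10% overall dropout.

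**What to change.** Replace the clause on the weight with wording such as: *each observed outcome is weighted by the inverse of its estimated probability of being observed, 1/(1 - dropout probability), taken from the logistic dropout model.* Add that the correction holds for missingness explained by the variables in that model. If a separate analysis plan exists, check that it carries the same definition.

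The cost is one corrected sentence and one short addition. No data, design or resource change is needed, and the planned unweighted comparison stays as it is.

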#### Reporting

Estimated treatment effects (odds ratio and incidence rate ratio) will be reported with 95% confidence intervals.

Descriptive statistics will be calculated for baseline and follow-up. No significance tests will be performed at baseline.

#### Ethical and Research Governance Approval

We have received ethical approval from the Human Sciences Research Council Research Ethics Committee (Protocol REC No.1/16/02/11). The Department of Health in South Africa has also provided approval for this study.

#### Project Timescales

The study will run for a period of 15 months beginning in March/April 2011 to June/July 2012.

## Discussion

The results of this cluster randomized trial will assist the Department of Health in South Africa decide on a health service policy that is underpinned by comprehensive approach to reduce alcohol consumption among patients with active TB. Ultimately, if this intervention model for alcohol reduction is successful, the cure rates for TB will be closer to the Strategic Plan to contain TB as a communicable disease which is highly contagious, and which at this point is still considered a "high burden disease", and with HIV co-infection HIV/TB are considered to have "double disease burden".

## List of abbreviations used

AUDIT: Alcohol Use Disorders Identification Test; CAGE: Cut Down, Annoyed, Guilty and Eye Opener (alcohol use disorders screening test); IMB: Information-Motivation-Behavioural Skills Model; NIAAA: National Institute on Alcohol Abuse and Alcoholism; SBI: Screening and Brief Intervention; TB: Tuberculosis; WHO: World Health Organisation
